#### Qualitative data

Following completion of *Lina*, focus groups and interviews will be conducted with both student participants and teachers who were involved to collect implementation and experiential data.

Focus groups and interviews will be audio recorded and anonymised transcripts will be the data subject to analysis. For the purpose of data analysis, transcripts for 3 interviews, 1 focus group with young people and 1 teacher focus group from each country will be translated initially and the UK, CZ and PT teams will collaboratively devise a coding framework. This framework will then be used to conduct first-level data analysis separately in each country. Data will then be collated and analysed together by UK, CZ and PT researchers collaboratively.

#### Implementation evaluation data

To further understand how *Lina* would be implemented as part of routine school activities, and to inform dissemination and further implementation strategies, an embedded implementation evaluation will be conducted both during the trial and after it is completed. The implementation evaluation will draw from multiple data sources, using a mixed methods design, to get a full insight into the barriers and facilitators that would affect *Lina* delivery and learn how to increase reach and improve roll out. This evaluation will be conducted across trial schools in all three countries.

The primary data sources will be:*Questionnaire measures completed by teachers*—Teachers from intervention classes will complete questionnaires on feasibility (“Feasibility of Intervention Measure”), acceptability (“Acceptability of Intervention Measure”) and appropriateness (“Appropriateness of Intervention Measure”) [42] after each episode/session of *Lina* to give feedback on each session. They will then also complete these measures at post-intervention timepoint to feedback on the intervention as a whole.*Implementation data provided by teachers*—Teachers from intervention classes will answer three broad questions on *Lina* “what went well?”, “what didn’t go well?” and “what could have gone better?”. These questions will be asked by the researcher after each session of *Lina* for immediate feedback on the delivery of that session. Teachers will also answer these questions, retrospectively, at the end of the intervention to give feedback on *Lina* as a whole.*Structured observations*—A researcher will be present to conduct structured observations of all *Lina* sessions. *Focus groups (teachers and psychologists)*—Following the completion of *Lina*, teachers will be invited to participate in focus groups to elaborate on their experience of implementation, and give interactive feedback on potential strategies to facilitate implementation.*Focus groups (young people)*—Students from intervention classes who experienced *Lina* will be invited to participate in focus groups where they can elaborate on their lived experience of using the intervention and how its delivery could be improved.

#### Data collection timepoints

The baseline measures will be completed after the class has been randomised, but prior to the beginning of the intervention.

Baseline measures will be collected *at least* 1 week before the first session of *Lina*. It is most likely that baseline data will be collected 2 weeks before the first *Lina* session, therefore allowing enough time to collect data from all students in the class.

Post-intervention measures will be collected between 8 and 10 weeks from the date of baseline assessments (allowing a 2-week time window, while accounting for the instances where classes hold multiple intervention sessions in a week). Six-month follow-up measures will be collected within 4 weeks (either side) of the date of six whole months since baseline assessments.

Measures will be completed as part of the routine school day, within a class session. If a participant is absent from school, or data is missing for any reason, then the research team will have 3 weeks from the data collection time point to collect that data.

All trial assessments will need to take place within the 2025/26 academic year. In the rare case that schools or classes are delayed in their delivery of *Lina* and final follow-up falls outside of the summer academic term then follow-ups may need to take place sooner than 6 months post baseline.

### Harms {17}

Participation involves low expected risk, e.g. emotional distress during data collection, safeguarding disclosures during the intervention or minor physical injury during classroom activities. Risks will be mitigated through the use of age-appropriate measures, clear information about voluntary participation and withdrawal and clear Standard Operating Protocols to guide researchers on how to identify and manage risks sensitively when working with adolescents, and delivery in schools with existing safeguarding support. Researchers will monitor participants throughout all activities and may pause or stop data collection if concerns arise. Clear procedures are in place to guide measured responses to any harm identified or reported and escalate concerns to school safeguarding leads where required. All adverse events are recorded (expected, unexpected, related or unrelated), with serious events reported promptly to the research leadership and ethics committees within 24 h.

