## Intervention and comparator

### Intervention and comparator description {15a}

#### Description of the intervention

The intervention under investigation *Lina* is a newly developed software-led program with accompanied in-person reflection designed to enhance students’ sense of belonging through a blended approach of interactive gameplay facilitated by smartphones in a classroom setting. All necessary equipment, including smartphones, routers, headphones and paper-based materials will be provided by the trial team to the class.

The intervention is primarily user-driven but will be guided by the classroom teacher (or a psychologist in the case of PT). Additionally, a researcher will be present during every session to make observational notes and support usage, where required. The intervention consists of six sessions. Four of these are “episodes” of the *Lina* story and will be delivered on a provided individual smartphone, while two will be “analogue” sessions, which are structured and interactive sessions within the classroom to enhance the sense of belonging and embed the psychotherapeutic principles inherent in the intervention. In CZ and the UK, it is typically teachers who will deliver the analogue sessions, in line with detailed lesson plans and provided materials. In PT the psychologist members of our team will deliver these sessions, in line with national legislation.

The order will be as follows:

Lesson 1: *Lina* episode 1.

Lesson 2: *Lina* episode 2.

Lesson 3: Analogue session 1.

Lesson 4: *Lina* episode 3.

Lesson 5: *Lina* episode 4.

Lesson 5: Analogue session 2.

During the smartphone-based sessions, each student plays a character in a fictional class. The four *Lina* episodes follow the story of a girl called Lina, a fictional classmate who abruptly left the school. Lina had been secretive, and at times, Lina’s behaviour seemed unusual or difficult to understand. The class collectively decides to uncover what happened to her. Players examine objects Lina left behind using augmented reality, revisit shared memories and piece together the story. By the last episode, they learn that Lina has been caring for her mother, who struggles with a poor mental health (low mood, guilt) that has profoundly affected their daily lives. Lina and her mother have moved to live with Lina’s aunt, allowing her mother to receive support while Lina returns to her previous school.

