#### Description of the comparator

Control classes will engage in standard school activities/routine lessons and will be provided the intervention in the beginning of the next school calendar year.

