### Concomitant care permitted or prohibited during the trial {15d}

As this is taking place within routine classes in schools, students and teachers will continue to receive all usual educational and wellbeing support delivered by schools. Given the vulnerable status of young participants in the trial, they will not be excluded from accessing additional interventions during the trial period. Information on the use of any additional support services availed of by students as a result of the trial within schools will be captured through trial assessments (e.g. Health Economics Inventory forms) and reviewed in the analysis to assess the cost of delivering the intervention in the schools.

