
#### Resource use data

We will collect three groups of data for resource use in the economic evaluation.First, we will collect data from teachers/psychologists on their time spent preparing and delivering *Lina* and usual sessions. The data will be collected for three periods, i.e. at baseline (with 3 months recall), the end of 8–10 weeks intervention (with 8–10 weeks recall for control group and weekly data collection for intervention group after each *Lina* session), and 6 months follow-up (with 6 months recall). In addition to time spent by teachers/psychologists, we will also collect data on other professionals’ time spent (e.g. administrative staff, teaching assistants) on delivering *Lina* or usual sessions. We developed four Health Economics Inventory forms for data collection on time spent by teachers/psychologists and other professionals.Second, our research team will collect data on the quantity and costs of equipment used for delivering *Lina* sessions, including smartphones, routers, headphones, and paper-based materials.Third, we will collect data on time spent by teachers/psychologists and other professionals (e.g. administrative staff, teaching assistants, counsellors) providing additional mental health/wellbeing support to students as well as managing students’ disruptive behaviours. The data will be extracted from school records for the period from 3 months before baseline till the end of 6 months follow-up.

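### Adverse-event capture is described as more intensive in the Lina arm than in the control arm, so raw counts by arm may be biased against Lina

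*Protocol article*

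**What the plan says.** **Detection and recording.** Harms {17} says "Researchers will monitor participants throughout all activities and may pause or stop data collection if concerns arise". It adds that "Clear procedures are in place to guide measured responses to any harm identified or reported", with escalation to school safeguarding leads where needed. All adverse events are to be recorded, whether or not expected and whether or not related.

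**Lina arm.** Under Description of the intervention, "The intervention consists of six sessions", and "Additionally, a researcher will be present during every session to make observational notes and support usage, where required". Implementation evaluation data repeats this: "A researcher will be present to conduct structured observations of all" Lina sessions. The same section has the researcher ask the teacher after each session what went well, what did not and what could have gone better.

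**Control arm.** "Control classes will engage in standard school activities/routine lessons" (Description of the comparator). No section places a researcher in those lessons or puts a matching question to control teachers.

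**Both arms.** There are three assessments: baseline, post-intervention and 6 months. Data collection for outcome measures has them facilitated by the class teacher or, in Portugal, a psychologist, with a researcher named for the UK and Czechia.

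**Use.** Interim analyses {28b} lets the TSC terminate the trial on regular reports that include adverse events. Under {28a} the TSC also acts as the data monitoring committee and reviews safety reports, such as the number of serious events.

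**The concern.** Recording unrelated as well as related events implies that both arms are covered. A count by arm can be read as a contrast only if an event has a similar chance of being noticed in each arm. Here one arm has an outside observer in the room for six lessons and a prompted conversation with the teacher after each. As described, the other arm relies in the same period on someone choosing to report.

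The counts go to a committee that can stop the trial, and harms would be expected in the final report. Even without a formal test, readers will set the two columns side by side. Without the source of each event, an excess under Lina could reflect closer observation, a real effect of the sessions, or both.

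**Working it through.** The protocol gives no adverse-event rate, count or capture probability, so there is no stated figure to reproduce. The check has two parts.

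**1. Described occasions on which trial staff are with a class**

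- Lina: 6 sessions + 3 assessments = 9.
- Control: 0 lessons + 3 assessments = 3.

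The zero for control lessons is inferred from silence. In Portugal a researcher at the assessments is not stated, but that applies to both arms alike. These numbers count opportunities to observe. They are not an expected ratio of events, because events can also be reported when no researcher is present.

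**2. What unequal capture could do to recorded counts when the true rates are equal**

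Let *s* be the share of events arising in the six lesson slots, *pL* and *pC* the probabilities that such an event is recorded in the Lina and control arms, and *c* the probability that an event arising at any other time is recorded, equal in both arms. The recorded ratio is

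R = [*s*·*pL* + (1 − *s*)·*c*] / [*s*·*pC* + (1 − *s*)·*c*].

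All inputs are assumptions; none is in the documents: *pL* = 0.9, *c* = 0.5, *pC* from 0.9 down to 0, and *s* = 0.10, 0.25 or 0.50.

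| *s* | *pC* = 0.9 | *pC* = 0.5 | *pC* = 0.2 | *pC* = 0 |
|---|---|---|---|---|
| 0.10 | 1.00 | 1.08 | 1.15 | 1.20 |
| 0.25 | 1.00 | 1.20 | 1.41 | 1.60 |
| 0.50 | 1.00 | 1.40 | 2.00 | 2.80 |

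Worked case, *s* = 0.25 and *pC* = 0.2:

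- Lina: 0.25 × 0.9 + 0.75 × 0.5 = 0.225 + 0.375 = 0.600.
- Control: 0.25 × 0.2 + 0.75 × 0.5 = 0.050 + 0.375 = 0.425.
- R = 0.600 / 0.425 = 1.41.

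Per 100 true events in each arm, that is 60 recorded under Lina against 42.5 under control.

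The top of the range depends on capping *s* at one half. At *s* = 0.75 and *pC* = 0 the formula gives (0.675 + 0.125) / 0.125 = 6.4. With equal true rates, though, that would need three quarters of control students' events over about six months to fall in six ordinary lessons, which is hard to credit. Even one half is generous.

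**The case against.** **No comparison is planned.** No section specifies a test or contrast of adverse-event counts. They serve oversight, and under {15b} the safeguarding ground for stopping a session or a student's participation is a concern related to the intervention, which is a judgement about cause. This stands. A reader might infer that Lina will look more harmful, but the documents support only that raw counts by arm, if read that way, may be biased.

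**Researchers are not the only route.** Harms {17} also covers harm that is reported, and school safeguarding operates in both arms. This stands too, and it rules out reading the 9 and 3 occasions as a threefold excess of events: that would require nothing to be recorded outside a researcher contact. But passive reporting in both arms does not cancel active observation in one.

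**Exposure is not detection bias.** Disclosures during the intervention can occur only where there is an intervention. Counting them under Lina is correct, which is a reason to report them separately.

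**Harm outside sessions is measured.** A reader might infer that it goes uncompared. It does not: PHQ-8, SAS-A, WHO-5, loneliness and the two quality-of-life scales are taken at the same three times in both arms ({18}) and compared by mixed models ({27a}).

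**The concomitant-care wording.** Section {15d} says "Information on the use of any additional support services availed of by students as a result of the trial within schools will be captured", which could be read as limiting harm capture to Lina. That text concerns the cost of delivery and is not a harms route, so it needs no change on this account.

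**Details may sit elsewhere.** The operating procedures are not shown and may set adverse-event reporting for control classes. If they do so on equal terms, the problem disappears. What the article does describe is uneven. Close observation of a new programme in minors is a defensible safety choice; the point concerns only how the resulting counts are compared.

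**Conclusion.** The concern holds in a limited form. As described, ascertainment is more intensive in the Lina arm and nothing offsets it, so raw adverse-event counts by arm are not like for like and may be biased against Lina. The direction follows from the design, provided that control lessons are unobserved and the unseen procedures do not equalise capture. The size cannot be determined: the range of about 1.0 to 2.8 rests wholly on assumed capture rates, equal true rates and at most half of events arising in the six lesson slots. Some of any excess may be a true consequence of taking part in Lina. The effectiveness analyses are untouched, and so is the review of individual events for safety. This is a cheap improvement to the harms section, not a fault in the design.

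**What to change.** In Harms {17}, state that:

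1. each adverse event is recorded with its source, meaning the route by which it first came to notice (an event seen in a Lina session and then escalated to the school counts as session-observed);
2. any comparison between arms, in TSC reports or the final report, uses only events captured the same way in both arms, namely those arising at the three assessments and those reported through school safeguarding;
3. events seen during Lina sessions or raised in the post-session questions are reported separately, as descriptive data for the Lina arm only.

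All events still go to the TSC as now.

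School-record data may be shown by arm as supporting information, since "The data will be extracted from school records for the period from 3 months before baseline till the end of 6 months follow-up". They hold staff time spent on support and disruptive behaviour, not events, so they should not be counted as adverse events.

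The cost is some protocol wording, a source field and a split table, with no extra staff or visits. Events already logged would need a source assigned from existing records. The downside is that fewer events enter the comparison, which makes it less precise. Some imbalance may also remain, because teachers know their class's allocation and may report differently.

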### Participant timeline {18}

**Table Tabb:** 

	**Trial period**			
	**Enrollment**	**Post-randomisation**		
**TIMEPOINT**^**b**^	*** − t***_***i***_** to 0**	***t***_***0***_*** (Baseline)***	***t***_***1***_*** (Post-intervention)***	***t***_***2***_*** (6 months)***
**ENROLLMENT:**	X			
**Eligibility screen**	X			
**Allocation/randomisation**	X			
**Informed consent**		X		
**INTERVENTION/COMPARATOR:**				
***Lina***** lessons**		X ––––––––- > X		
**Routine school lessons**		X ––––––––- > X		
**ASSESSMENTS** **(YOUNG PEOPLE):**				
**Demographics**		X		
**Delaware School Climate Survey- Student**		X	X	X
**WHO-5 Well-being Index**		X	X	X
**Patient Health Questionnaire-8**		X	X	X
**Social Anxiety Scale for Adolescents (SAS-A)**		X	X	X
**University of California Los Angeles (UCLA) Loneliness Scale**		X	X	X
**Social-Emotional Learning Edition of the Strengths and Difficulties Inventory System [brief version] (SSIS SELb)**		X	X	X
**Peer Mental Health Stigmatisation Scale-Revised (PMHSS-R)**		X	X	X
**Health-related Quality of Life EQ-5D-Y-3L**		X	X	X
**Child Health Utility-9D (CHU-9D)**		X	X	X
**Intervention (*****Lina*****) feedback**			X	
**Interviews and Focus Groups**			X	
**ASSESSMENTS (TEACHERS):**				
**Demographics**		X		
**Health Economics Resource Inventory**		X	X	X
**Implementation evaluation form (Feasibility, Acceptability, Appropriateness)**			X	
**Intervention (*****Lina*****) feedback**			X	
**Focus Groups**			X	

### Sample size {19}

#### Size of trial sample

Based on an assumed small to medium effect size (Cohen’s *d* = 0.4) based on school mental health meta-analyses [43], and a conservative Intraclass Correlation Coefficient (ICC) of 0.1 [44], which takes into account the clustering at the class and school level, and a design effect of 2.7, 40 classes per country will provide 90% power (alpha = 0.05).

The analysable trial sample assumes an average cluster size of 18 (a total of 720 participants per country). To allow for an anticipated drop-out rate of 20%, an average cluster size of 22 will be recruited at baseline (i.e. average 22 adolescents per classroom), thus giving a total sample size of 880 per country. The cluster size of 22 at baseline takes into account the variability in class sizes within and across each country, and expected number of participants who opt out of the study.

#### Size of interview and focus group sample

For the post-trial interviews and focus groups it is predicted that there will be a maximum of 160 young people per country invited to participate in the evaluative qualitative work (up to 120 young people invited to a focus group, and 40 young people invited to be interviewed).

For teachers, there is predicted to be 20 teachers per country eligible to be interviewed or invited to a focus group.

### Recruitment {20}

#### Sampling technique

In order to recruit 40 classes per country, we predict that around 10 schools per country will need to be recruited, with each contributing an average of 4 class cohorts. We anticipate there will be variations in the number of class cohorts available within individual schools across countries.

This will represent an overall opportunistic sampling method, making use of schools who have indicated an interest in the *Lina* and have agreed to become a flagship school. However, we will aim to purposively recruit schools with higher levels of deprivation as deprivation is linked to greater risk of poor mental health.

In PT, the percentage of Free and Reduced Cost School Meals will be used as an indicator of deprivation. Young people who come from the lowest economic socioeconomic status have free lunches (they are listed as A in the school support system) and young people from low, but slightly higher, socioeconomic status families pay 50% of the lunch (and they are listed as B in the school support system).

We will aim to recruit schools with the highest numbers of students listed in category A for Free and Reduced School Meals.

In CZ and the UK, schools will be recruited near to the respective research bases (University of Birmingham and Masaryk University), which both reflect urban areas, with high numbers of relatively disadvantaged schools. Although priority will be given to pragmatic considerations (ease of access, eagerness of school to participate), local knowledge will be used to preferentially shift recruitment towards more disadvantaged schools. In the UK, this is reflected by schools having a higher-than-average proportion of students meeting the low socioeconomic status criterion for additional school funding from the government (“pupil premium”), as available on government websites (≈ > 30%). In both countries, it is reflected by relatively high levels of ethnic minority students, as ascertained based on local knowledge.

#### Recruitment of schools

Schools will be identified, approached and recruited across the three countries using a number of different strategies that are adapted to the national context. In general, the trial team will make use of existing networks, conferences, seminars and learning events attended by headteachers and teachers to promote the study, and assess interest. Those schools that want to support the study will be offered to become a “flagship school” to support in the networking within educational networks about the intervention and the objectives of the trial. Flagship schools will be given the opportunity to become a trial school (i.e. a trial site from which we recruit classes and participants from), but this will not be mandatory.

